### Ethics

The study will be conducted in accordance with the ethical guidelines as described in the Helsinki—declaration (Declaration of Helsinki, 2013). The Regional Committee for Medical and Health Research Ethics has approved the study protocol (REK: 2016/340). Patients will receive both written and oral information about the study, before they are asked to give their written consent to participate. All data will be stored according to approval. Both of the two treatment modalities offered are well-established psychotherapy methods in which patients have responded, on average, equally well. The treatment are manualized [11, 32]. The therapists are experienced and specifically trained, and the therapies will be supervised throughout the study period. Patients who do not wish to participate in the study will receive treatment as usual at Nydalen and Vinderen outpatient clinics, Oslo, Norway. The patients are informed that they can withdraw from the study whenever they want to, and that this will have no consequences for their further treatment at the outpatient clinic.

### User involvement

A service user with relevant diagnosis and experience of therapy have been recruited to participate in the formation of the qualitative study interview and give feedback on the general structure, implementation and conduction of the study from a patient participants point of view.

### Eligibility criteria

#### Inclusion criteria

Inclusion criteria are currently fulfilling the criteria of a MDD according to the DSM-IV (based on a clinical interview and MINI), age 18–65 years, the ability to understand, write and speak a Scandinavian language, and willingness and ability to give informed consent.

#### Exclusion criteria

Exclusion criteria are current or past neurological illness, traumatic brain injury, current alcohol and/or substance dependency disorders, psychotic disorders, bipolar disorder type 1, developmental disorders, and mental retardation. Patients are not excluded for other comorbid psychiatric conditions in order to capture a representative sample of depressed individuals.

### Patients

Patients are recruited among patients referred with depressive symptoms to two outpatient clinics in Oslo, South Eastern health region, Norway (Nydalen DPS, and Vinderen DPS). Recruitment commenced at Nydalen Outpatient Clinic, Oslo University Hospital (OUS) in January 2017, while Vinderen psychiatric outpatient unit, Diakonhjemmet hospital startet recruiting patients June 2018. In total one hundred patients will be recruited Fig. 1.

**Fig. 1 Fig1:**
[figure not shown]
Flow diagram describing the MOP study: randomized controlled trial comparing cognitive behavioral therapy and psychodynamic psychotherapy

### Randomization procedures and methods used to minimize bias

#### Recruitment and baseline procedures

The patients are first screened for inclusion and exclusion criteria. Patients eligible for the study are given oral and written information about the project and are invited to a second interview after 2–3 days. Where written consent is obtained, baseline assessment commences.

When these assessments have been completed a trial ID is assigned and patients are allocated to one of the two therapies. To minimize bias, the design is single blind, i.e. outcome assessors at pre and post treatment and further follow-up evaluations will not be aware of assigned study condition. If blindness is broken, all subsequent assessment will be carried out by an alternative evaluator [36].

### Assessments and outcomes

The baseline and follow up clinical examination will be conducted by a group of experienced clinicians who will complete a training and reliability program at the Division of Psychiatric Treatment Research, Oslo University Hospital. In addition, the raters will receive supervision on a regular basis by experienced raters and clinician. Consensus meetings will be held in order to assure reliability of assessments.

### Pre-treatment

#### Interviews

Before randomization each patient is diagnosed according to the DSM-IV criteria using the M.I.N.I. [54] and the SCID II [34]. The Psychodynamic Interview (PI) modified after Malan and Sifneos [60, 73] is used to assess psychological functioning through the Psychodynamic functioning scale (PFS) [46]. The PFS consists of 6 scales that explore Quality of family relationships, Quality of friendships, Quality of romantic/sexual relationships, insight, tolerance for affect and problem solving and adaptive capacity. The psychodynamic interview also taps quality of object relations (QOR-2 relations to others and relation to family). The Depression Specific Reflective Functioning interview (DSRF) [71] is used to assess reflective functioning, and the Global Assessment of Psychosocial Functioning (GAF) addresses level of functioning and symptom severity [70]. Hamilton Depression Rating Scale (HDRS) [39] assesses level and characteristics of depression.

#### Self-report

An extensive battery of self-report questionnaires is used; The Working Alliance Inventory (WAI-SR_1) [43] assess alliance, the Experience in Close Relationships (ECR) [20] evaluates attachment style and Inventory of interpersonal problems (IIP-64) [2] taps interpersonal distress. The Structural Analysis of Social Behaviour (SASB) [37] also assess interpersonal and intrapsychic interactions, and Severity Indices of Personality Problems-Short Form (SIPP-SF) [82] is used to assess personality problems.

Questionnaires that assess childhood trauma, Childhood Trauma Questionnaire (CTQ) [17], work and social adjustment, WSAS [65], emotional awareness/alexithymia, the Toronto Alexithymia scale (TAS-20) [4] will also be used at several time points during therapy and at follow up.

Metacognitions are assessed using Meta Cognitive Questionnaire (MCQ-30) [85], cognitive insight using Becks Cognitive Insight Scale (BCIS) (Aaron T. [13], dysfunctional attitudes using the Dysfuntional attitude scale (DAS) [14] Rumination related scales are used, including the Positive Beliefs about Rumination Scale (PBRS) [69] Negative Beliefs about Rumination Scale (NBRS) and Ruminative Response Scale (RRS) [78].

Depressive symptoms are assessed using Becks Depression Inventory (BDI) [15] and manic/hypomanic symptoms using Hypomania Checklist-32 [3]. Levels of anxiety are assessed using GAD-7 [74]. In addition sociodemographic are recorded and health related quality of life is assessed by Short-Form 12 (SF-12) [84].

### During therapy

During therapy the patients are assessed with self-report questionnaires at weeks 3, 8, and 16. At 3 weeks, the WAI-SR_1 is used.

At 8 weeks, the WAI-SR_1, SIPP-SF, WSAS, GAD-7, TAS-20, BDI, PBRS, NBRS, SAS, ECRI, MCQ-30, RRS, BCIS and DAS are used.

At 16 weeks, WAI-SR_1, SIPP-SF, TAS-20, BDI, PBRS, NBRS, WSAS, GAD-7, SASB, ECR, RRS, MCQ-30, BCIS and DAS are used.

### Post treatment

At the end of treatment patients are interviewed and assessed by the same team of evaluators as in the pre-treatment assessment. The patients are interviewed using the M.I.N.I. to ascertain if they still satisfy the diagnostic criteria for a current depressive episode. The posttreatment assessment also includes the Psychodynamic Interview (PI), The Depression Specific Reflective Functioning interview (DSRF), Global Assessment of psychosocial Functioning (GAF) and Hamilton Depression Rating Scale (HDRS).

Most of the self-report questionnaires from the baseline assessments are used, including the WSAS, SF-12, BDI, SIPP-SF, TAS-20, PBRS, NBRS, SAS, ECR, MCQ-30, RRS, BCIS, GAD-7, DAS, IIP-64 and HCL-32. In addition sociodemographic variables are recorded.

### Follow up assessments

#### 1 year follow up

The M.I.N.I interview will be used to ascertain if the patient still satisfy the diagnostic criteria for a current depressive episode. The 1 year follow up also includes the Psychodynamic Interview (PI), The Depression Specific Reflective Functioning interview (DSRF), Global Assessment of psychosocial Functioning (GAF) and the Hamilton Depression Rating Scale (HDRS).

Most of the self-report questionnaires from the baseline assessments are used, including the WSAS, SF-12, BDI, SIPP-SF, TAS-20, PBRS, NBRS, SAS, ECR, MCQ-30, RRS, BCIS, GAD-7, DAS, IIP-64 and HCL-32. In addition sociodemographic variables are recorded.

#### 3 year follow up

The MINI interview will be used to ascertain if the patient still satisfy the diagnostic criteria for a current depressive episode. The 3 year follow up also includes the Psychodynamic Interview (PI), The Depression Specific Reflective Functioning interview (DSRF), Global Assessment of psychosocial Functioning (GAF) and the Hamilton Depression Rating Scale (HDRS).

Most of the self-report questionnaires from the baseline assessments are used, including the WSAS, SF-12, BDI, SIPP-SF, TAS-20, PBRS, NBRS, SAS, ECR, MCQ-30, RRS, BCIS, GAD-7, DAS, IIP-64 and HCL-32. In addition, sociodemographic variables are recorded.

## Intervention: CBT compared to PDT for treatment of patients with MDE

### Therapists

The psychotherapy with CBT and PDT are conducted by therapists from Nydalen and Vinderen psychiatric outpatient clinic, who have completed a minimum of two-year training in CBT and PDT. In addition, all therapists receive specific training in the CBT and PDT study manuals prior to commencing as therapists in the study. All treatment sessions are videotaped and independent psychiatrists will carry out assessment of treatment fidelity on a selection of random tapes.

### Treatments

Patients are randomized to 16 weekly sessions of CBT followed by 3 monthly booster sessions, or 28 weekly sessions of PDT. This approach was chosen in an attempt to design the study as close to clinical practice as possible (ecological validity). In designing the study, we discussed this issue with both experienced clinicians and psychotherapy researchers. They seemed to agree that it was no firm clinical or empirical evidence to have more than 19 sessions of CBT and too little with less than 28 sessions of PDT. However, both arms have the same measurements point (during therapy, at end of therapy (28 weeks) and at the 1 and 3 years follow-up). This approach is in line with other studies comparing CBT and PDT [35]. All sessions last 45 min.

#### Psychodynamic psychotherapy (PDT)

Short-term psychodynamic psychotherapy (STPP) is a well-known treatment mode. The dynamic therapy in MOP is based on the general psychodynamic principles described by Gabbard [32]. The STPP manual used in the First Experimental Study of Transference–Interpretations [45] describes the specific features for time-limited therapy used in the trial. A case formulation is made in collaboration with the patient during the first sessions, describing (1) symptoms and problems, (2) precipitating stressors or events, (3) predisposing life events or stressors, (4) mechanisms that links preceding categories together, and finally 5) what to focus in the therapy The time-limited approach is further specified in guidelines for patient-information at the start of treatment. The dynamic treatment is mainly exploratory in nature. Patients are encouraged to explore sensitive topics and repetitive interpersonal patterns, including exploration of the patient-therapist relationship [79]. Exploration and interpretation of transference, i.e. linking interpersonal patterns to transactions between the patient and the therapist will be used with moderate intensity.

#### Cognitive behavioural therapy (CBT)

Cognitive therapy for depression by Beck et al. [11] will be used as treatment manual. The CBT manual describes the goal directed framework of the intervention. The first sessions will focus on the therapeutic alliance and engagement of the patients to therapy. Psychoeducation will be provided. The intervention will focus on both short and long term goals. Different cognitive techniques, described in the manual, will be applied to reach these goals. The last part of therapy will focus on consolidation and relapse prevention.

### Statistical analysis plan

An causal graph (DAG) of mediation is shown in Fig. 1, with randomized treatment $$A$$ that corresponds to the two treatment groups in MOP, mediator $$M$$, outcome $$Y$$ that corresponds to symptoms of depression, and mediator-outcome confounders $$C$$. The longitudinal nature of the data in MOP, is well suited to assess mediation, in that group assignment can, with certainty temporally precede the mediator which again one can be sure of temporally precedes the outcome, to assure causal effects. Repeated assessments, both on the mediator and symptoms of depression, can be used to generalize the simple setting with one assessment of each. The basic concepts are easiest illustrated in the simple setting. Traditional methods to study mediation have important limitations concerning interactions and non-linearities [9], in contrast to the counterfactual-based approach, which is able to decompose a total effect of treatment on the outcome into indirect effect (through the mediator), and direct effect (direct relative to the mediator), even in the presence of an interaction between treatment and mediator. It can be argued that the interaction term should be included, even if it’s not statistically significant. In order to specify assumptions and identifiability of effects, the following definitions of indirect / direct effects are needed. In general, let $${a}^{*}$$ and $$a$$ be t**w**o levels of treatment, here the two groups of CBT or PDT.

$$CDE\left(m\right)$$: The controlled direct effect expresses how much symptoms of depression would change on average if the mediator where fixed at level $$m$$ uniformly in the whole population, but the treatment group where changed from $${a}^{*}=0$$ to $$a=1$$

$$NDE$$: The natural direct effect expresses how much symptoms of depression would change if the treatment were set at level $$a=1$$ versus level $${a}^{*}=0$$, but for each individual the mediator were kept at the level it would have taken, for that individual, if she had been in the reference group ($${a}^{*}=0$$) (effect of treatment group assignment on symptoms of depression, that would remain if the pathway from treatment to mediator were disabled).

$$NIE$$: The natural indirect effect expresses how much symptoms of depression would change on average if the treatment group were fixed at $$a=1$$, but the mediator were changed from the level it would take if $${a}^{*}=0$$ to the level it would take if $$a=1$$ (effect of treatment group assignment on symptoms of depression that operates by changing the mediator).

Simple regression models will suffice to estimate the direct and indirect effects above, but some confounding control assumptions are needed. Randomization of treatment group guarantees unbiased estimation of total effect of treatment group on symptoms of depression, but not unbiased estimation of direct / indirect effects [81]. In order to be able to estimate the $$CDE\left(m\right)$$, an assumption of no unmeasured confounding for the mediator—depression relationship is needed (all confounders are measured and controlled for). This is also a necessary assumption to be able to estimate $$\mathrm{NDE}$$ and $$\mathrm{NIE}$$. In addition, no mediator- depression confounder should be affected by treatment group assignment (the dashed arrow in Fig. 2 has to be absent). If such an influence (arrow) is plausible, the natural direct and indirect effects are not identifiable. The controlled direct effect can still be identified with a structural mean model (SMM), and estimated by g-estimation (Vansteelandt 2016).

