An attempt to uncover mechanisms of change in CBT was reported by Rush and colleagues already in 1981, when they examined 35 patients with depression who received CBT or an antidepressant. They found that changes in cognitive processes predicted significantly lower depression scores at follow up in the CBT group but not in the antidepressant group. They suggested that this could indicate an indirect support for the cognitive theory of depression [72]. This is in line with several other studies that have examined how cognitive processes might mediate outcome among patients with a depressive disorder. In a study by Kaufman and colleagues examining eight potential mediators, they found that changes in negative automatic thoughts were related to outcome in CBT for adolescents with depression. However, they had only pre and posttest assessments making inferences of causality difficult [50]. Tang and DeRubeis found that change in cognitions was followed by less depressive symptoms in the following sessions [77].

Furthermore, a number of studies have shown that CBT is associated with reduced negative automatic thoughts and that these changes co-vary with depressive symptomatology [7, 67, 87]. However, these aforementioned studies mostly did not examine if cognitive change happened before the changes in mood (temporality), or whether the changes were specific for CBT. It could be that negative automatic thoughts are a product of depression rather than a cause of depression.

As summarized in Bergin and Garfield’s Handbook of Psychotherapy and Behavior Change [53], theory of change in CBT is proposed as change in dysfunctional attitudes, underlying schemas and compensatory skills. However, no adequate test of these mediators has been done to date. Previous studies are limited by not including a control/comparison group, inadequate sample size, and furthermore fail to assess the mediator before the symptom change. Bergin and Garfield conclude that further studies should examine which variables mediate the effects of CBT and to what degree such variables are specific to CBT.

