## Causal inference in randomized groups

Methods in causal inference have rapidly developed over the last decades, and are now widespread in most fields, both in social science and medicine. They are also useful to assess mechanisms and effect heterogeneity (variation across individuals) between treatment and outcome. The relevant causal concepts are mediation and interaction, in which the counterfactual-based approach has become standard, in line with the book of VanderWeele [81]. A counterfactual-based approach involves “potential outcomes” to conceptualize causation, by conceiving of what might have occurred had the treatment been otherwise than it was. If the outcome would have been different due to a different treatment, then it is meant that the treatment “causes” (affects) the outcome. Although it is difficult to draw causal conclusions for individuals based on a dataset, one can make inference about such effects on average for a population under specific assumptions. A necessary assumption in mediation is temporality. Repeated measures allows for ensuring that the treatment precedes the mediator, which again precedes the outcome.

Methods for mediation can help to understand mechanisms and pathways through intermediates in a causal effect of treatment on an outcome. The motivation to assess mediation can be interest in refinement in a treatment intervention. This might be done by improving components in the treatment that target a particular mechanism. Before proceeding with such a refinement, it is desirable to know the extent to which the mechanism targeted is an important pathway from treatment to outcome. Empirical studies of mediation may help to assess relative importance of various mechanisms.

Effect heterogeneity is often explained by an additive interaction, or moderation (prescriptive factor), when different subgroups of individuals defined by one variable somehow alters the treatment effect, the moderator being the variable that defines the subgroups. Additive interactions can help to determine which subgroups would benefit most from a treatment method or even if it is harmful for some. Assessing interaction can also shed light on mechanisms themselves [81].

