#### Mediators of change

Does improvement occur through different or similar change processes (mechanisms) in the two treatment modalities?

We will test the following theoretically based hypotheses:In CBT symptom and functional improvement will be mediated by changes in negative automatic thoughts, dysfunctional attitudes, attributional styles, underlying cognitive schemas, and the learning/development of compensatory skills.In PDT symptom and functional improvement will be mediated by improved self-understanding/insight and emotional awareness, less harsh self-view, more adaptive personality functioning, more mature defense mechanisms, and increased reflective functioning.

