### Trial status

Protocol version 2 (November 2018). The first patient was included February, 2017. The study is ongoing and has recruited 63 patients (February, 2020). The last patients will be assessed three years after end of treatment in December 2023 (Table 1).

**Table 1 Tab1:** Overview: assessments administered at research baseline and each follow-up point throughout the trial

Assessment points	Interviews	Self-report questionnaires	Therapist questionnaires
Baseline (0 weeks)	M.I.N.I., SCID-II, PFS, DSRF, GAF, Hamilton	SF-12, WSAS, CTQ, BDI, SIPP-SF, TAS-20, PBRS/NBRS, SASB, ECR, MCQ-30, RRS, GAD-7, BCIS, DAS, IIP-64, HCL-32	WAI, FWC-58, Therapist adherence
After session 3		WAI	WAI, FWC-58
After session 8		SF-12, WSAS, WAI, BDI, SIPP-SF, TAS-20, PBRS/NBRS, SASB, ECR, MCQ-30, Rumination scale, GAD-7 BCIS, DAS	WAI, FWC-58
After session 16		SF-12, WSAS, WAI, BDI, SIPP-SF, TAS-20, PBRS/NBRS, SASB, ECR, MCQ-30, Rumination scale, GAD-7, BCIS, DAS,	WAI, FWC-58
After 28 weeks/post treatment	M.I.N.I. (depression module only) PFS, DSRF, GAF, Hamilton	SF-12, WSAS, WAI, BDI, SIPP-SF, TAS-20, PBRS/NBRS, SASB, ECR, MCQ-30, Rumination scale, GAD-7, BCIS, DAS, IIP-64, HCL-32	WAI, FWC-58
1 year follow up	M.I.N.I.(depression module only) PFS, DSRF, GAF, Hamilton	SF-12, WSAS, BDI, SIPP-SF, TAS-20, PBRS/NBRS, SASB, ECR, MCQ-30, Rumination scale, GAD-7 BCIS, DAS, IIP-64, HCL-32	
3 year follow up	M.I.N.I. (depression module only), GAF, Hamilton	SF-12, WSAS, BDI, SIPP-SF, TAS-20, PBRS/NBRS, SASB, ECR, MCQ-30, Rumination scale, GAD-7 BCIS, DAS, IIP-64, HCL-32	

WAI-SR_1, Working Alliance Inventory; WSAS, The Work and Social Adjustment Scale; SF-12, The 12-item Short Form Health Survey; CTQ, Childhood Trauma Questionnaire; BDI, Beck Depression Inventory; SIPP-SF, Severity Indices of Personality Problems-Short Form; TAS-20, Toronto Alexithymia Scale; PBRS, Positive Beliefs about Rumination Scale; NBRS, Negative Beliefs about Rumination Scale; SASB, Structural Analysis of Social Behaviour; ECR, Experiences in Close Relationships Inventory; MCQ-30, The Metacognitions Questionnaire 30; RRS, Ruminative Responses Scale; BCIS, Beck Cognitive Insight Scale; GAD-7, Patient Health Questionnaire; DAS, Dysfunctional Attitude Scale; IIP-64, Inventory of interpersonal problems; HCL-32, Hypomania Checklist-32

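### The article says the mediator is sure to precede the outcome, but its visit schedule does not support this for all hypothesised mediators, reflective functioning above all

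*Protocol article*

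**What the plan says.** The section Causal inference in randomized groups sets the standard: "A necessary assumption in mediation is temporality". The Statistical analysis plan then states that the design meets it, in that "group assignment can, with certainty temporally precede the mediator which again one can be sure of temporally precedes the outcome". The sentence concerns the mediator in general and makes no exception.

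Under Mediators of change the article undertakes to test two sets of hypotheses. Improvement in CBT is to be mediated by "changes in negative automatic thoughts, dysfunctional attitudes, attributional styles, underlying cognitive schemas, and the learning/development of compensatory skills". Improvement in PDT is to be mediated by "improved self-understanding/insight and emotional awareness, less harsh self-view, more adaptive personality functioning, more mature defense mechanisms, and increased reflective functioning". Counting insight and emotional awareness separately, that is 5 CBT and 6 PDT mediators.

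The primary outcome is depressive symptoms on the HDRS and BDI-II. The week-28 interview cell of Table 1 reads "M.I.N.I. (depression module only) PFS, DSRF, GAF, Hamilton": the interviews that rate insight and reflective functioning take place at the visit where the HDRS is scored. No interview is scheduled between baseline and week 28.

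**The concern.** The article expects the two therapies to be equally effective and makes moderators and mediators the purpose of the planned analysis. Whether a mediator is measured before the outcome is therefore central to the trial.

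If a mediator and the end-of-treatment outcome are first re-measured at the same visit, their association cannot separate a mechanism of recovery from a consequence of it. Under the present wording, a concurrent association between reflective functioning and symptoms at week 28 could be reported as mediation with temporal order assured by design. The article sees the problem in others' work: of an earlier study of cognitive mediators it says that "they had only pre and posttest assessments making inferences of causality difficult".

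A second, less certain issue is that some constructs on the list of hypotheses have no named measure, so a reader cannot tell how they would be tested.

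**Working it through.** The article gives no figure on this point, so the check is a cross-tabulation. Inputs are the mediators under Mediators of change, the instruments under Pre-treatment, and the visits under During therapy, Post treatment, Follow up assessments and Table 1.

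| Mediator | Therapy | Instrument in the article | Weeks 8 and 16? |
|---|---|---|---|
| Negative automatic thoughts | CBT | none named | no |
| Dysfunctional attitudes | CBT | DAS | yes |
| Attributional styles | CBT | none named | no |
| Underlying schemas | CBT | none of their own; DAS as partial proxy | only through DAS |
| Compensatory skills | CBT | none named | no |
| Self-understanding/insight | PDT | PFS insight scale, or BCIS | PFS no, BCIS yes |
| Emotional awareness | PDT | TAS-20 | yes |
| Self-view | PDT | SASB (inferred) | yes |
| Personality functioning | PDT | SIPP-SF | yes |
| Defense mechanisms | PDT | none named | no |
| Reflective functioning | PDT | DSRF | no |

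Three notes on the mapping:

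- The article describes the BCIS as a measure of cognitive insight but does not say whether it or the PFS is the insight mediator.
- The SASB is described as covering interpersonal and intrapsychic interactions; its use for self-view is my inference. The week-8 text prints SAS where Table 1 has SASB, and I read these as the same instrument.
- The background section on mediators counts dysfunctional attitudes among the components of cognitive schemas, which is the case for letting the DAS stand for schemas.

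Counts out of 5 + 6 = 11:

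| Mapping | Measured at weeks 8 and 16 | Interview visits only | No named instrument |
|---|---|---|---|
| Insight = PFS, schemas separate | 4 | 2 | 5 |
| Insight = BCIS | 5 | 1 | 5 |
| Insight = BCIS, schemas = DAS | 6 | 1 | 4 |
| Insight = PFS, SASB not accepted for self-view | 3 | 2 | 6 |

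Each row sums to 11. Accepting the SASB, four to six mediators have a mid-treatment measure; rejecting it under the PFS mapping gives three. Even the most generous row leaves 11 − 6 = 5 without one.

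Timing for reflective functioning: the DSRF is given at baseline, week 28 and 1 year. At 3 years the text includes it but Table 1 does not. Its first post-baseline value coincides with the week-28 HDRS and BDI. Change from baseline to week 28 therefore covers the same interval as symptom change over treatment and cannot be ordered before it. The same value does precede the 1-year and 3-year outcomes. The PFS follows the same pattern.

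The HDRS is also absent at weeks 8 and 16. Only the BDI gives repeated symptom scores during treatment.

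**The case against.** Several stronger readings are tempting, and the article does not support them.

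- **Exactly four mediators have a mid-treatment measure and two have only interview-visit measures.** This holds under one mapping. The BCIS is scheduled at weeks 8 and 16, and the DAS covers part of what the article calls schemas. A range is the honest statement.
- **The temporality claim is false for most mediators.** For a construct with no named instrument the question is measurement, not order. For the DSRF and PFS, order fails for the week-28 outcome but not for follow-up. The demonstrable order failure concerns one or two mediators at one outcome time.
- **The trial repeats the pre/post weakness it criticises.** Not quite: the DSRF and PFS are also taken at follow-up, which a purely pre/post study lacks. The likeness is confined to the treatment period.
- **Measurement favours PDT mechanisms.** A reader might infer this from 1 of 5 CBT mediators against 3 of 6 for PDT under the first mapping. It depends on that mapping and ignores the other cognitive measures repeated at weeks 8 and 16 (PBRS, NBRS, RRS, MCQ-30). Mediators from both therapies are also to be tested in both arms.
- **Some hypotheses cannot be tested at all.** The article condenses a full protocol that may name further instruments or ratings from the session videotapes, although the only tape rating it describes is treatment fidelity. The PFS problem-solving scale might be offered for compensatory skills. That would move one construct from the last column to the middle one and leave the mid-treatment count unchanged.

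It can also be said that the sentence describes a generic diagram with one mediator and does not promise order for each one. That is fair as to wording. But it is given as a property of this trial's data, without exception, and the article itself calls temporality necessary. The timing objection therefore stands: the article fixes these visits explicitly, so condensation does not explain it.

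**Conclusion.** The temporality statement is too strong as written. It fails for reflective functioning, and for insight if rated by the PFS, when the outcome is symptoms at week 28. It can be supported for about four to six of the eleven mediators, those with a week-8 and week-16 measure. This assumes that the SASB measures self-view; the upper end also assumes that the BCIS measures insight and the DAS stands for schemas.

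The lack of a named instrument for negative automatic thoughts, attributional styles, compensatory skills and defense mechanisms is a weaker finding. It is true of the article, but the full protocol could settle it. The timing finding does not depend on that document unless it adds in-treatment ratings that the article's schedule does not show.

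**What to change.** 1. Limit the temporality statement in the Statistical analysis plan to mediators measured at weeks 8 and 16, and use those values to predict later BDI-II scores.
2. For the DSRF and PFS insight, test change from baseline to week 28 against 1-year HDRS and BDI-II, adjusted for the week-28 symptom score. Do not claim mediation of end-of-treatment improvement for these two.
3. Add a table tying each mediator under Mediators of change to one instrument and its visits. State whether insight means the BCIS or the PFS, and whether the DAS stands for schemas.
4. If a construct proves to have no measure in the full protocol, do not present it as a mediation test.

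The cost is rewording and a reordered analysis of visits already scheduled. The scientific price is that reflective functioning and PFS insight then speak only to symptom change after treatment, and some theory-based hypotheses may have to be dropped. Under item 2 the week-28 symptom score may itself be affected by the assigned therapy. By the article's own identification conditions, natural direct and indirect effects would then not be available, and its g-estimation route to the controlled direct effect would be needed. Adding instruments late is no full remedy: 63 of 100 patients had been recruited by February 2020, and self-report baselines not collected from them cannot be recovered.
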